#### Sample Size Calculation for Regression Analysis

Regression analysis will be applied to assess the relationship between engagement and demographic factors (eg, age and gender). This will assist in the identification of predictors of engagement and potential subgroup effects [97]. These analyses are exploratory and may be underpowered. For linear regression, a common rule of thumb suggests 15-20 participants per predictor variable [98,99]. For logistic regression, a minimum of 10 outcome events per predictor variable is typically required [100].

A total of 600 participants will provide sufficient sample size power for multiple predictors while ensuring a balanced distribution across intervention arms. This sample size also accounts for expected variability in engagement behavior across arms and balances analytic rigor with the practical realities of digital recruitment.

#### Sample Size for Repeated Measures

Since engagement data will be collected across multiple time points, generalized estimating equations will be used to account for within-subject correlations. The generalized estimating equation is well-suited for analyzing longitudinal behavioral data in real-world digital environments, allowing more accurate estimation of SEs and robust modeling of repeated engagement behavior. A within-group correlation of ρ=0.3 was assumed, based on prior studies of engagement in digital health. This estimate aligns with findings from longitudinal analysis in behavioral health studies that report moderate within-person correlation of repeated engagement measures [101,102]. A 15% attrition rate was factored into the final sample size, suggesting an adjusted recruitment target of 100 participants per arm to maintain statistical power.

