### Our Prior Work

We have experimented with nudges and prompts in the past. In our previous 3-arm randomized controlled trial (RCT) [24], arm 1 featured a member home page without nudges or prompts. Arm 2 featured a home page with a tip-of-the-day section. Arm 3 featured a home page with a tip-of-the-day section and a to-do checklist.

Control arm members (1788/13,224, 13.52%) completed an average of 1.5 course components. Arm 2 members (865/13,224, 6.54%) clicked on 5% of tips and completed an average of 1.8 course components. Arm 3 members (1914/13,224, 14.47%) clicked on 5% of tips, completed 2.7 of 8 to-do checklist items, and an average of 2.11 course components. Completion rates in arm 2 were greater than those in arm 1 (*z* score=3.37; *P*<.001), and completion rates in arm 3 were greater than those in arm 1 (*z* score=12.23; *P*<.001). Engagement in all 8 components in arm 3 was higher than that in arm 2 (*z* score=1.31; *P*<.001).

Further analysis confirmed that behavioral economics techniques, such as nudges and prompts, significantly enhance engagement in digital health interventions. Specifically, users in the nudge + prompt condition (arm 3) were 93% more likely to engage compared to those in the control group (arm 1), as indicated by an odds ratio of 1.93 (95% CI 1.71-2.17; *P*<.001). This increase in engagement was reflected across multiple platform activities, including self-assessments, goal setting, and content interaction.

However, while these findings validate the effectiveness of nudges and prompts, the study did not explore how individual-level factors shaped these outcomes. Specifically, we did not examine how the intersection of demographic characteristics and cognitive or behavioral phenotypes influenced engagement, if individual engagement followed properties of power laws [61], or if we could leverage economic tools such as the Gini coefficient to plot participation inequality [62].

Understanding these patterns is important for optimizing future interventions for full personalization and maximizing the effectiveness of digital health tools.

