### Power and Sample Size

The primary outcome of interest is engagement, measured through click-through rates, session duration, and to-do checklist completion rates across the 6 experimental arms. These metrics allow us to assess how different combinations of prompts and gamification elements affect user behavior. This will help us determine which strategies are most effective for sustaining participation in self-guided programs.

The study is designed to detect small to moderate effect sizes in engagement differences between intervention groups. Expected effect sizes range from Cohen f=0.1 (small) to f=0.25 (moderate). Our goal is to obtain a power of 80% (β=.20) and a significance level of .05 (α) to ensure adequate sensitivity in detecting meaningful differences between groups.

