#### Sample Size Calculation for ANOVA

Given that engagement metrics will be compared across 6 arms, a one-way ANOVA test was used to estimate the required sample size. For a small effect size (f=0.1), approximately 86 participants per arm (a total of 516 participants) are required. For a moderate effect size (f=0.25), approximately 28 participants per arm (a total of 168 participants) are required. These calculations assume normality of residuals and homogeneity of variance for ANOVA-based analysis. Chosen effect sizes are based on prior research in digital health engagement studies [94-96]. In our prior RCT [23,24], engagement data were analyzed using mixed-effect logistic regression, which does not rely on these assumptions.

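### ρ=0.3 is stated for the GEE but plays no visible part in the 100 per arm, so the claim that 100 per arm keeps 80% power is not supported for that analysis

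*Protocol article*

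**What the plan says.** The general section on power sets 80% power, α of .05 and effects from f=0.1 to f=0.25. In the ANOVA subsection, "a one-way ANOVA test was used to estimate the required sample size", and for f=0.1 "approximately 86 participants per arm (a total of 516 participants) are required".

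The repeated-measures subsection then says that engagement will be recorded on several occasions and analysed by GEE. It adds "A within-group correlation of ρ=0.3 was assumed, based on prior studies of engagement in digital health", cites 15% attrition, and ends by "suggesting an adjusted recruitment target of 100 participants per arm to maintain statistical power". The Sample Size Justification section carries this forward as 600 participants with adequate power.

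**The concern.** A within-user correlation affects a sample size only together with m, the number of observations per user. The article gives ρ but no m, design effect or variance factor. The only adjustment it cites on the way to 100 per arm is attrition. So the subsection presents ρ as a design input and GEE as the model, while the number appears to come from a design with one value per participant.

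The power claim attached to 100 per arm is therefore a claim about the GEE that the stated steps do not establish. A null GEE result at the small end of the planned effect range would be read against 80% power that was not shown for that model.

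**Working it through.** **Inputs.** Six equal arms, α=.05, 80% power, f=0.1 and 0.25, 86 per arm, ρ=0.3, 15% attrition and 100 per arm all come from the Protocol article. The value of m is not given, so a range is shown.

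**Step 1: reproduce the 100.** 86/0.85 = 101.2 and 86 × 1.15 = 98.9. Either is about 100, and ρ is not needed. In reverse, 100 × 0.85 = 85 contributing users per arm, 510 in total.

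**Step 2: check the 86.** For a one-way ANOVA, use the noncentral F with 5 and N−6 degrees of freedom and λ = N·f². At f=0.1, 80% power needs 215 per arm (1,290 in total). With 86 per arm, power is 37%. With 85 per arm and one observation each, 80% power is reached only at f of about 0.16.

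**Step 3: bring in ρ and m.** For a time-averaged arm effect with exchangeable correlation, the variance factor is (1+(m−1)ρ)/m, so λ = N·f²·m/(1+(m−1)ρ). Example for m=4 and N=510: the factor is (1+3×0.3)/4 = 0.475, and λ = 510 × 0.01/0.475 = 10.74. Results for f=0.1 per observation and ρ=0.3:

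| m | factor | λ, 510 users | power, 510 users | power, 600 users | recruits per arm for 80%, with 15% attrition |
|---|---|---|---|---|---|
| 1 | 1.000 | 5.10 | 36.6% | 42.9% | 253 |
| 2 | 0.650 | 7.85 | 55.0% | 63.2% | 165 |
| 3 | 0.533 | 9.56 | 64.9% | 73.2% | 136 |
| 4 | 0.475 | 10.74 | 70.8% | 78.9% | 122 |
| 5 | 0.440 | 11.59 | 74.6% | 82.3% | 112 |
| 7 | 0.400 | 12.75 | 79.2% | 86.3% | 103 |
| 8 | 0.3875 | 13.16 | 80.7% | 87.5% | 99 |

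80% is first reached at m=8 with 510 users and at m=5 with 600.

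**Step 4: vary f and ρ.** At f=0.25 with 85 per arm, power is above 99% at m=1. At f=0.1 and ρ=0.1, m=4 suffices for 85 per arm. At ρ=0.5, no m reaches 80% with 85 or 100 per arm.

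**Step 5: find the source of the shortfall.** The factor equals 1 at m=1 and is below 1 for every larger m. Starting from a correct single-observation size, leaving ρ out can therefore only overstate the n needed for this arm effect. The low power in the table comes from starting at 86 when the ANOVA needs 215.

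**The case against.** The strongest reply is that a single-observation size is a safe bound for this GEE test. If 86 were a correct ANOVA figure, 100 per arm would keep about 80% power or more at any m, as the article says. This stands: the power loss belongs to the 86. What remains is that the text offers ρ as an input without using it, and that the power claim fails at f=0.1 for small m.

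A second reply is that a condensed article may leave m and the GEE formula to the full protocol. That is fair as far as it goes, and a missing m alone would not be a finding. But the article does state an input, a model, a number and a power claim, and as stated they do not connect. The route from 86 to 100 is inferred because no formula is printed; both usual attrition adjustments lead there.

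One might also suppose that 86 already includes ρ, since the GEE needs 87 per arm at m=7. The article attributes 86 to a one-way ANOVA and gives no m, so this does not show that ρ was used.

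Three stronger readings are tempting, and the document supports none of them:

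- *That omitting ρ causes the underpowering.* Step 5 shows the opposite direction for a time-averaged effect.
- *That m must be about 2 because prior users completed 1.5 to 2.11 course components.* Completed components are an outcome. The Data Collection section also records prompts that were displayed but not clicked, and these are observations too.
- *That click comparisons between arms can never reach 80%, taking the 5% tip click rate with the odds ratio of 1.93.* That odds ratio is for overall engagement against a control without tips, and both prior tip arms clicked 5% of tips. The prior trial reported no such contrast.

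**Conclusion.** The point holds in a limited form. The 100 per arm is accounted for by the ANOVA figure and attrition, ρ=0.3 does no work in the stated derivation, and the claim of maintained power is unsupported for the GEE.

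At f=0.1 and ρ=0.3, power ranges from 37% to 81% as m goes from 1 to 8 with 510 users. These figures assume exchangeable correlation, an arm effect constant over time, and f on the scale of a single observation. If f instead refers to a per-participant summary such as a click rate, the dependence on m does not apply and power at f=0.1 with 85 per arm stays at 37%. It would be wrong to say without these conditions that the trial needs eight observations per user: five suffice if all 600 contribute, and one suffices at f=0.25.

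**What to change.** In the repeated-measures subsection, state that 100 per arm was obtained from the ANOVA figure and attrition only. Then do one of the following:

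- Replace the closing claim about power with the GEE power at 510 users, f=0.1 and ρ=0.3 for the number of observations expected per user, and state that number.
- Remove ρ=0.3 as an input and give the power that 85 per arm has with one observation per user: 37% at f=0.1.

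Make the change together with the correction of 86 in the ANOVA subsection, since that figure is the source of the shortfall, and bring the Sample Size Justification section into line. The cost is a few sentences and one short calculation. Restating the power needs no extra participants. The stated power at f=0.1 will be less favourable unless users contribute several observations each.

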#### Sample Size Justification

To ensure the predictive model has sufficient training data, the study aims to recruit a minimum of 600 participants (100 per arm). This sample size balances feasibility with analytic rigor, ensuring adequate power to detect differences in engagement and to train AI-driven predictive models. Refer to Multimedia Appendix 1 for the study’s CONSORT-SPI (Consolidated Standards of Reporting Trials-Social and Psychological Interventions) checklist [103].

### Data Collection

The Evolution Health platform is equipped with a custom data collection interface and reporting mechanism. Data will be collected for each member who is randomly assigned to the experiment, and all data are self-reported. Information on age and self-identified gender will be collected at registration or during secure sign-on across various white-label instances.

The custom database will also track behavioral engagement with each tip and to-do item randomly presented to users, including whether a tip was displayed, whether it was clicked, and whether the user completed the corresponding course component.

### Engagement Metrics: Operational Definitions

Engagement is defined as follows:

Click rate is defined as tips or checklist items that users click on.Tip interaction is considered “complete” when a user clicks on a tip and completes an exercise.Gamification metrics (eg, progress bar status, quiz completion, badge acquisition) will be recorded as binary variables (earned vs not earned).Session duration is calculated as the elapsed time (in seconds) between a user logging in and logging out of the platform.

### Ethical Considerations

All data collection policies and procedures adhere to international privacy guidelines, including the General Data Protection Regulation, the US Health Insurance Portability and Accountability Act, where applicable, and the Declaration of Helsinki [104-107]. At registration, all members endorse a checkbox confirming that they consent to have their data used for research purposes and approve the platform’s privacy policy.

The platform does not collect personally identifiable information except a user’s email address, which is required for registration confirmation, retrieval of lost passwords, and two-factor authentication. Email addresses are encrypted and stored in a separate database.

This study is conducted on a self-guided resiliency course for displaced Ukrainian refugees, but it does not measure clinical outcomes. While participants are randomized into 6 intervention arms, the study is classified as an RCT, but it is not an RCT under medical research standards [108]. To clarify, this study adheres to principles of an RCT, where participants are randomly assigned to conditions, but does not fall under medical trial classification as it does not measure health outcomes. The CONSORT-SPI guidelines for social and psychological intervention trials will be followed [103].

The primary outcome variable being tested is course engagement, not wellness or symptom reduction. The study does not evaluate whether participant engagement with course tools improves mental health or reduces emotional stress related to forced displacement. Any potential clinical effects of engagement strategies tested in this study will require investigation in future research.

Since this study does not measure clinical outcomes, it does not fall under ClinicalTrials.gov or the WHO International Clinical Trials Registry Platform requirements. However, to ensure transparency, the trial was registered with Open Science Framework, a widely recognized registry for social science and behavioral health research.

As the study was based on deidentified user data and did not collect medical or clinical measures, it was deemed exempt from further review by Evolution Health’s Institutional Review Board. This exemption is per regulatory standards for minimal-risk research involving nonidentifiable behavioral data.

## Results

This protocol was designed in January 2025. α and β testing of the intervention are scheduled to begin in July 2025, with a soft launch anticipated in August 2025. The experiment will remain active until the sample size requirements are met. Live monitoring and periodic data quality checks will be conducted throughout the study duration.

## Discussion

### Hypothesis

From our previous study, we anticipate higher engagement in arms that include the to-do checklist, particularly when combined with gamification (arm 6) or social proof tips (arm 5) (H1 and H2). Previously, these combinations demonstrated higher click-through and completion rates in earlier research. We expect similar trends in this trial, though results may vary based on population characteristics and platform context.

The study will also contribute to the development of AI models capable of predicting and optimizing user engagement, allowing for the customized delivery of to-do items and tips based on behavioral phenotypes (H2). These models will be trained using the behavioral data collected across study arms. Ultimately, this approach aims to enhance long-term adherence by tailoring interventions to individual patterns of use.

In our previous research on user engagement within the platform’s social network, we observed that engagement patterns followed power law distributions [88]. A follow-up study found that demographic and condition-specific characteristics did not predict social network engagement [89]. However, this study will help determine whether course engagement follows similar power law properties or if age and gender are predictive of engagement outcomes, particularly given the inclusion of session duration and behavioral phenotypes as new analytical factors (H3).

### Expected Results

This study builds on prior RCT findings, extending the use of behavioral economics to underserved, culturally sensitive populations. Unlike existing studies by platforms, our focus on mental health and refugees offers unique contributions to both research and practice. Findings may also advance AI-driven personalization in digital health.

### Strengths and Limitations

A strength of this experiment is that it will be conducted in an ad libitum environment. Unlike most digital health studies, it will not be conducted with a small population in a controlled environment. Further, members will not be aware of the experiment, which will limit participant bias and the Hawthorne effect.

Based on stratified randomization, which will balance demographic factors, the dataset generated will enable predictive analytics for adaptive engagement strategies. Other indication-specific data, such as results and qualifying criteria from the mental health screener [81], have the potential to enrich tailoring. These layers of data will help evolve the platform from static guidance toward real-time personalization.

A limitation of this experiment is that, especially due to the anonymity of members, we have no way of confirming user identity. Registrants may be displaced Ukrainians, individuals reviewing the program based on general interest, researchers, practitioners reviewing the platform for professional use, Evolution Health competitors, industry analysts, or other users who may not be engaging with the platform to help achieve wellness. Sensitivity analyses will be conducted to filter and exclude anomalous user engagement data.

Although engagement correlates with improved intervention outcomes, this study does not measure wellness improvements. Follow-up research will be required to establish clinical efficacy.

### Future Directions

By leveraging randomized experiments and AI, this study provides a blueprint for scalable, culturally sensitive digital health interventions based on demographic characteristics, indication-specific variables, and behavioral phenotypes. This methodology allows for the continuous refinement of engagement strategies over time. The framework can be adapted to support different populations and health indications across diverse settings.

Engagement data from this trial will serve as the foundation for training predictive analytics models that identify which behavioral prompts are most effective for specific user profiles. These models will help personalize the delivery of content in real time, increasing the likelihood of user interaction. Over time, this data-driven approach may significantly improve long-term platform engagement.

As data volume increases (training and validation data), models will be refined and validated using new user cohorts, allowing us to optimize recommendations and nudge strategies based on user behavior, language, and engagement patterns. This iterative refinement process will enhance model accuracy and reduce overfitting. It also enables better generalization across diverse user segments and use cases.

This adaptive approach will also support future deployment of the course in additional languages and for other displaced populations. The underlying platform is designed to be modular, making translation and cultural adaptation straightforward. This scalability is essential for addressing global mental health disparities across diverse regions.

### Conclusions

This trial represents a novel approach to behavioral health research by leveraging randomized experimentation to develop AI-ready behavioral datasets. By targeting an underserved, international, and culturally sensitive population, it contributes critical insights toward scalable, personalized digital mental health interventions. Findings may help inform future digital health efforts that aim to improve engagement, accessibility, and long-term adherence.

## Appendix

Multimedia Appendix 1 CONSORT (Consolidated Standards of Reporting Trials)–Social and Psychological Interventions checklist.

## Abbreviations

AI: artificial intelligence
CBT: cognitive behavioral therapy
LLM: large language model
NAMI: National Alliance on Mental Health
NIMH: National Institute of Mental Health
RCT: randomized controlled trial
SAM: serviceable available market
SOM: serviceable obtainable market
TAM: total addressable market
WHO: World Health Organization
